## Abstract

**Background:**

Venous thromboembolism (VTE) is a significant public health issue, with a rising global incidence despite extensive research efforts. Patient-centered care, which tailors treatment to individual needs, has shown potential in enhancing outcomes. The integration of smart technologies with psychological frameworks such as the health belief model and the knowledge-attitude-practice (KAP) model may further improve patient engagement and adherence. To address this, we have developed a smart technique–assisted patient-centered care mobile health app for managing VTE (mVTEA), which integrates psychological frameworks to improve patient outcomes in VTE management.

**Objective:**

This study aims to investigate the impact of the mVTEA app on the knowledge, attitudes, and practices of VTE in patients with or at high risk of VTE.

**Methods:**

The SmaVTE (smart technology facilitated patient-centered venous thromboembolism management) study is a 2-armed, single-center, parallel-group, randomized controlled trial. A total of 256 hospitalized patients with or at high risk of VTE will be recruited on the day of their discharge from August 2024 to June 2025. Participants will be randomly allocated to either the mVTEA management group or the routine management group in a 1:1 ratio. The mVTEA management group (n=128) will receive patient-centered VTE management facilitated by the mVTEA app after discharge. The routine management group (n=128) will be administered conventional postdischarge management according to local clinical practice. The KAP of patients will be assessed by a structured KAP questionnaire on VTE. The primary outcome is the difference in patients’ KAP on VTE at 3-month follow-up between the 2 groups. Secondary outcomes include scores on each domain of the questionnaire, quality of life, VTE events, chronic thromboembolic pulmonary hypertension, chronic thromboembolic pulmonary disease, postpulmonary embolism syndrome, major bleeding events, VTE-related hospitalizations or rehospitalizations, deaths, and new-onset atrial fibrillation or atrial flutter at 3-month follow-up.

**Results:**

Participants are currently being recruited. The first participant was enrolled in August 2024, which marked the official start of the study. The recruitment process is expected to be completed in June 2025. As of the submission of the paper, 185 patients had been enrolled in this clinical trial. At present, all included patients are being followed up according to the outlined schedule.

**Conclusions:**

The SmaVTE study offers a pioneering approach to VTE prevention and treatment by combining smart technology with patient-centered care and established theoretical frameworks. The findings could significantly impact clinical practice and inspire further research into the integration of smart technologies with behavioral science theories.

**Trial Registration:**

ClinicalTrials.gov NCT06350331; https://clinicaltrials.gov/study/NCT06350331

**International Registered Report Identifier (IRRID):**

DERR1-10.2196/67254

## Introduction

### Background

Venous thromboembolism (VTE), which encompasses deep vein thrombosis and pulmonary embolism (PE), affects more than 1 in 12 individuals over their lifetime and poses a substantial health and economic burden [1-4]. Despite decades of research on the prevention and treatment of VTE, the prevalence of VTE has substantially increased worldwide [5-7]. Up to 75% of VTE cases occur in the hospital or within 90 days after hospital discharge [2,8], highlighting the complexity and challenge of VTE management.

Studies suggest that many prescribed pharmacologic prophylaxes are not administered due to patient refusal or insufficient patient-nurse communication [9-12]. Even among patients who commence anticoagulant therapy, many discontinue treatment after bleeding or other setbacks. Clinicians also face the difficult task of balancing thrombosis and bleeding risks, which often share overlapping risk factors that can change over time [13,14]. Determining an optimal, individualized decision is therefore fundamental to improving VTE management.

Patient-centered care, recommended by cardiovascular guidelines [15,16], emphasizes meeting patients’ unique needs and involving them in decision-making. Adoption of a patient-centered approach has demonstrated benefits in cardiovascular disease, improving patient knowledge, self-efficacy, and health outcomes [17,18]. A limited number of studies suggest similar benefits in VTE management [19-21], but further research is needed on the role of patient-centered care for patients with or at risk of VTE.

Smart technology, such as wearable devices, mobile health (mHealth) apps, artificial intelligence, and digital communication platforms, has shown potential in facilitating patient education, providing real-time feedback, and enhancing patient engagement [22-24]. The use of smart technology in patient-centered care supports personalized and proactive health care by empowering patients to manage their health, which is especially important for VTE, where patient behavior greatly affects outcomes [13,16,25]. A cohort study has shown that an mHealth-based web-based anticoagulation management system can effectively improve patient care and safety for warfarin-treated patients with VTE [26].

Although mHealth is effective, patient engagement tends to wane over time [27,28]. Furthermore, studies on health behavior suggest that simply emphasizing risk does not necessarily promote better adherence, due to psychological phenomena such as “optimistic bias” [29,30]. Various theoretical models have been advanced to explain health behaviors, with the health belief model (HBM) being one of the most common [31-34]. Studies demonstrate that HBM-based interventions can enhance self-management [33]; yet, their ability to predict health behaviors is limited [35]. The knowledge-attitudes-practices (KAP) model offers complementary insights, linking knowledge to behavioral attitudes, and thereby representing another potentially useful tool [32,34]. To the best of our knowledge, there is a lack of research in the field of VTE that integrates the theories of HBM and KAP, complemented by mHealth technology.

To address this research gap, we have recently developed a smart technology–assisted, patient-centered care mHealth app for managing VTE (mVTEA) [36]. Its goal is to improve patient-centered care for patients with or at risk of VTE by combining HBM and KAP frameworks.

### Objective

The SmaVTE (smart technology facilitated patient-centered venous thromboembolism management) study aims to investigate the impact of the mVTEA app on the KAP of patients with or at high risk of VTE assessed by a VTE-KAP questionnaire in a 3-month randomized controlled trial. We hypothesized that this theory-based mHealth intervention can improve the KAP of these patients while ensuring their safety compared to traditional face-to-face medical visits.

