### Outcome Measures

#### Primary Outcome

The primary outcome of this study is the difference in patients’ KAP on VTE at 3-month follow-up between the mVTEA management group and the routine management group.

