#### Secondary Outcomes

Secondary outcomes include scores on each domain of the VTE-KAP questionnaire (knowledge domain, attitude domain, practice domain), QoL, VTE events, chronic thromboembolic pulmonary hypertension, chronic thromboembolic pulmonary disease, post-PE syndrome [13,48], International Society on Thrombosis and Hemostasis (ISTH) defined major bleeding events [59], VTE-related hospitalizations, VTE-related rehospitalizations, all-cause deaths, PE-related deaths, and new-onset of atrial fibrillation (AFI) or atrial flutter (AFL) at 3-month follow-up. For patients with more than 1 event, only the first event will be counted. A total of 3 investigators who are unaware of patients’ group assignments will adjudicate all endpoints.

Generic, nondisease-speciﬁc health-related QoL is assessed using the EQ-5D-5L questionnaire and its corresponding visual analog scale [60]. Brieﬂy, the EQ-5D-5L generates an overall index that ranges from 0 (lowest generic QoL) to 1 (highest generic QoL) and is calculated based on country-speciﬁc reference value sets. The EQ-5D-5L health index was calculated with the value set for China. The EuroQol visual analog scale ranges from 0 to 100, with higher scores indicating better health.

VTE events are categorized into 3 groups: new-onset VTE, hospital-acquired VTE (HA-VTE), and recurrent VTE. VTE that occurred for the first time during the study period is classified as new-onset VTE. HA-VTE is defined as any new-onset VTE that has occurred within 90 days of hospital discharge [4]. Recurrent VTE is defined as the appearance of new evidence of VTE after acute VTE has been treated in the acute phase (2 weeks) with significant clinical improvement in signs and symptoms. According to the time of VTE recurrence, it is further categorized into early VTE recurrence (within 3 months after the last VTE occurrence) and late VTE recurrence (more than 3 months after the last VTE occurrence) [61]. Hospitalization due to the new-onset VTE will be documented as VTE-related hospitalizations, while rehospitalization due to VTE recurrence, progression, or complications arising from VTE treatment will be classified as VTE-related rehospitalizations. All-cause death refers to any death occurring during the study period, regardless of the cause. PE-related death is defined as death explicitly caused by PE.

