### Statistics

#### Sample Size and Power Considerations

This study used a stratified block randomization method with 4 strata. Literature suggests an average of 50-100 patients per stratum for stratified randomization [63]. Previous studies in China have reported that the coefficient of variation for VTE-KAP questionnaire scores among patients at risk of VTE ranges from 0.1 to 0.12. In this study, a coefficient of variation of 0.1 was assumed, enrolling 50 patients per stratum, resulting in a total of 200 patients (100 per group). At a 2-sided significance level of .05, this design yields 94% statistical power to detect a 5% difference in VTE-KAP questionnaire scores between the two groups. Even with a 2-sided significance level of 0.025, the setup maintains 90% statistical power to detect the same 5% difference. Considering a 20% nonresponse rate, the final sample size was adjusted to 64 patients per stratum, leading to a total of 256 patients (128 in each group). The sample size was calculated by using Power Analysis and Sample Size software (version 19.4.1; NCSS, LLC).

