#### Statistical Analyses

In this study, we define 2 analysis populations: full analysis set (FAS) and intention-to-treat (ITT). FAS is the set of all patients who have received VTE prevention and treatment intervention at least once after randomization. The ITT set will include all randomly assigned patients, regardless of whether they completed the study or followed the study protocol. FAS will be the primary analysis population, and ITT will provide supportive results. Missing data will be handled using the multiple imputation method. Since the study outcomes already include assessments of safety data, the safety analysis set is not performed. Sensitivity analysis will be conducted by comparing the results of the ITT and FAS analyses.

Continuous variables will be presented as mean and SD, or as median and IQR for variables not following a normal distribution. Categorical variables will be presented as counts and percentages. Differences in baseline demographic and clinical characteristics, as well as survey data between groups, will be assessed using the Student *t* test or the Mann-Whitney *U* test for continuous variables, depending on distributional assumptions. Categorical variables will be analyzed using the chi-square test or Fisher exact test, as applicable.

To account for the repeated measurements of EQ-5D-5L and KAP survey data collected at discharge and the 3-month follow-up, we will use a linear mixed-effects model for repeated measures. The model will include fixed effects for the treatment group (mVTEA management vs routine management), time point (discharge vs 3-month follow-up), the interaction between treatment group and time point, the baseline score of the respective survey (EQ-5D-5L or KAP), and the prestratification factors (VTE diagnosis status at discharge: Yes or No; age: ≥60 years vs <60 years). Patients and their hospitalization units will be included as random effects. The key parameter of interest for evaluating the intervention effect over time will be the group-by-time interaction term. The Cox proportional hazards model will be used to compare the hazard of the event (time to event) between groups during the follow-up period, taking into account the prestratification factors. The hazard ratio and its corresponding 95% CI will be calculated using this model. Statistical significance is set at *P*<.05 (2-sided). SPSS (version 22.0; IBM Corp) will be used for statistical analysis.

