## Discussion

### Expected Outcomes

The SmaVTE study is an innovative study designed to address the multifaceted challenges of VTE management through the integration of smart technology. This trial aims to evaluate the effectiveness of the mVTEA app in VTE management, which is an mHealth app designed to enhance patient-centered care through the joint use of HBM and KAP theoretical frameworks. This study hypothesizes that such theory-based mHealth interventions can improve the KAP level for patients with or at risk of VTE while ensuring their safety compared to traditional face-to-face VTE management.

Unlike previous mHealth studies that focused mainly on patients with warfarin therapy, targeting patients with AFI and heart valve disease [26,64-66], the SmaVTE study expands the target population to include both patients at risk for VTE and those already diagnosed, as well as patients using direct oral anticoagulants (DOACs). This comprehensive scope is designed to reflect real-world clinical practice and address emerging challenges associated with DOAC management, such as renal impairment, drug interactions, and the absence of specific reversal agents [45,67]. Integrating the ABCDEF pathway into the KAP framework further supports a comprehensive and dynamic approach to VTE care, encompassing not only anticoagulation management but modifiable risk factors, long-term complications, and comorbidities. If proven effective, findings from this trial may have significant implications for clinical practice, supporting more proactive and personalized approaches to VTE prevention and treatment.

The theoretical foundation of the mVTEA app is grounded in the principles of patient-centered care and behavioral science theories. Patient-centered care emphasizes tailoring medical care to individual patient needs, preferences, and values [15,16]. Behavioral science theories, such as the HBM and the KAP theories, suggest that empowering patients with information and involving them in their care can significantly enhance motivation and adherence to treatment protocols [31-34]. The mechanisms by which the mVTEA app may influence behavior change can be attributed to several factors, including goal setting, real-time feedback, personalized reminders, and tailored health education programs. These features are designed to facilitate continuous engagement and allow patients to monitor their progress, thereby enhancing motivation and adherence.

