### Limitations

There were some limitations to this study. First, the applicability of the results may be confined to the population studied and may not fully extrapolate to other patient groups, such as those with AFI or heart valve disease. Second, the study encompasses only those patients who can use smartphones or computer tablets, which introduces a potential bias related to the participants’ digital literacy. To mitigate this effect, standardized training on the application’s use will be provided following the patient’s registration on the mVTEA app. Third, the experimental protocol could not implement double blinding, a limitation inherent to the specificity of mHealth interventions. To ensure the reliability of the data, blind statistical analysis will be conducted, and roles among interventionists, efficacy evaluators, and statisticians will be distinctly segregated. Finally, the clinical outcomes, designated as secondary endpoints in this study, require validation through subsequent research.

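### Comparative safety is part of the stated hypothesis, but the design as stated offers only a difference test on few events, with no margin, so a nonsignificant result could be misread as confirming safety

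*Protocol article*

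**What the plan says.** The Objective section states a joint hypothesis: the app "can improve the KAP of these patients while ensuring their safety compared to traditional face-to-face medical visits". The Expected Outcomes section of the Discussion repeats the safety clause: "while ensuring their safety compared to traditional face-to-face VTE management".

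The design is built on KAP. Under Primary Outcome: "The primary outcome of this study is the difference in patients’ KAP on VTE at 3-month follow-up". Under Sample Size and Power Considerations: "At a 2-sided significance level of .05, this design yields 94% statistical power to detect a 5% difference in VTE-KAP questionnaire scores", followed by "Even with a 2-sided significance level of 0.025, the setup maintains 90% statistical power to detect the same 5% difference". That section mentions no clinical event.

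Secondary Outcomes lists VTE events, chronic complications, ISTH major bleeding, VTE-related hospitalizations and "all-cause deaths, PE-related deaths, and new-onset of atrial fibrillation (AFI) or atrial flutter (AFL) at 3-month follow-up". Statistical Analyses compares the hazard of events between groups with a Cox model adjusted for the stratification factors, gives a hazard ratio with 95% CI, and sets significance at two-sided P<.05. It adds: "Since the study outcomes already include assessments of safety data, the safety analysis set is not performed". No margin, acceptable-risk bound or expected event rate is stated.

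Limitations says that "the clinical outcomes, designated as secondary endpoints in this study, require validation through subsequent research".

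**The concern.** Saying that an intervention improves one thing while ensuring safety against a comparator is a claim of being no worse. A two-sided difference test can show harm or benefit. When it is not significant, it cannot by itself show that harm has been excluded. That takes an interval judged against a bound set beforehand, and enough events to make the interval narrow.

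The article states the hypothesis, the basis of the sample size and the significance rule, and the three do not fit together. By dispensing with a safety set because safety is already among the outcomes, it also leaves these same event comparisons to carry the safety conclusion.

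The patients have VTE or are at high risk of it, and the pathway in Table 1 includes remote monitoring of anticoagulation with less need for in-person visits. Unsupported reassurance on bleeding, VTE or death would matter here.

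**Working it through.** **Step 1. The plan's own figure.** Inputs from Sample Size and Power Considerations: 100 per group, coefficient of variation 0.10, difference 5%, two-sided alpha .05 or .025.

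Standardized difference = 0.05/0.10 = 0.5. Power ≈ Φ(0.5·√(100/2) − z), where 0.5·√50 = 3.536.

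- alpha .05: Φ(3.536 − 1.960) = 94.2% (94.0% with the noncentral t).
- alpha .025: Φ(3.536 − 2.241) = 90.2% (89.8% with the noncentral t).
- Nonresponse: 200/0.8 = 250, or 62.5 per stratum. Rounding each stratum up to full blocks of 4 gives 64, and 4 × 64 = 256.

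The stated 94%, 90% and 256 reproduce. They concern KAP only.

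**Step 2. What the same sample gives for events.** The article gives no event rate, so the 3-month control risk p is **assumed** to be 2%, 3%, 5% or 10%. Each arm has 128 patients, with no loss to follow-up.

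- *Cox test, Schoenfeld approximation, true hazard ratio 2.* App-arm risk = 1 − (1 − p)². Expected events D = 128·[p + 1 − (1 − p)²]. Power ≈ Φ(√(D/4)·ln 2 − 1.96). Worked case p = 2%: D = 128 × (0.02 + 0.0396) = 7.63; √1.907 × 0.693 = 0.957; Φ(−1.003) = 16%.
- *Fisher exact test, p against 2p.* Exact enumeration, two-sided .05.
- *Expected upper 95% limit of the hazard ratio if the true value is 1.* Events E = 2 × 128 × p; limit = exp(1.96·√(4/E)). Worked case p = 2%: E = 5.12; exp(1.96 × 0.884) = 5.65.

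| Assumed control risk | Cox power, hazard ratio 2 | Fisher power, doubled risk | Events if no difference | Upper 95% limit if no difference |
|---|---|---|---|---|
| 2% | 16% | 7% | 5.1 | 5.7 |
| 3% | 21% | 12% | 7.7 | 4.1 |
| 5% | 32% | 24% | 12.8 | 3.0 |
| 10% | 56% | 55% | 25.6 | 2.2 |

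With 100 evaluable per arm, the same Cox formula gives 13% at a 2% risk (D = 5.96) and 46% at 10% (D = 29.0).

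**Step 3. Events needed.** Excluding a hazard ratio of 2 with 80% power at one-sided .025 needs 4·(1.960 + 0.842)²/(ln 2)² = 65.3, so 66 events. About 5 to 26 are expected over the assumed range.

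**Step 4. Dependence on the margin.** For noninferiority on the risk difference (80% power, one-sided .025), n per arm = (1.960 + 0.842)²·2p(1 − p)/margin². At p = 2%, a 2-point margin needs 770 and a 5-point margin needs 124. At p = 5%, a 5-point margin needs 299. These margins only illustrate the dependence and are not proposals. Whether 128 per arm is enough turns on a margin and a rate that the article does not give.

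**The case against.** The other side has a good case on several points.

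- **No rule equates nonsignificance with safety.** A reader might infer that P≥.05 will be reported as proof of safety. The article never says so, and its Limitations section points the other way. What can be said is that the result could be read like that.
- **Interval estimates are already planned.** Statistical Analyses provides hazard ratios with 95% CIs and counts for categorical variables, and defines an ITT set of all randomized patients, though as supportive. Much of the remedy is therefore in place.
- **The main aim is KAP.** Safety is a subordinate clause, and sizing a trial on its primary outcome is ordinary.
- **Some tempting extensions fail.** One might infer that the app arm replaces in-person follow-up. Table 1 speaks only of reducing the need for visits and also lists regular check-ups, and the 3-month follow-up may be an outpatient visit. Nor is the 3-month horizon a fault in itself, because the objective is set at 3 months.
- **An unseen SAP may set a margin.** The article refers to one.

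These points narrow the concern but do not remove it. The safety clause appears twice as part of the hypothesis. The Limitations caveat does not withdraw it or say how a null result will be interpreted. A planned interval shows safety only when judged against a bound, and none is stated. A SAP could add a bound, but it would not change the published hypothesis or the sample size of 256.

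**Conclusion.** The point stands as a mismatch between hypothesis and design. Comparative safety is hypothesized, but the stated inference on events is a difference test in a trial sized for KAP, with no margin or bound. A nonsignificant result would not support the safety half.

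The size rests on assumed control risks of 2% to 10% and full follow-up of 128 per arm. Power for a doubling is then about 16% to 56% (Schoenfeld) or 7% to 55% (Fisher), and under no true difference the data would on average leave hazard ratios up to about 5.7 to 2.2 unexcluded.

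It would be too strong to say that 256 patients could never address safety. At a 2% risk, a wide 5-point margin would need 124 per arm, just within 128 before nonresponse. The supportable statement is that the design as stated does not address it. The KAP sample size calculation is not in question.

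**What to change.** 1. In the Objective and Expected Outcomes sections, limit the confirmatory hypothesis to KAP and describe safety as a descriptive objective.
2. For major bleeding, VTE and death, report in all randomized patients the event counts per arm, the already planned hazard ratio with 95% CI, and the risk difference with 95% CI. The risk difference is the added item.
3. State that P≥.05 on these outcomes will not be taken as evidence that safety is preserved.

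The cost is wording and a reporting rule; no new data or patients are needed. The downside is that the sponsor gives up a safety claim that the design as stated does not support.
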